#### Lifestyle advice

For the purpose of the INFORM study, we are using a web-based lifestyle intervention for CHD prevention based on an intervention that was originally developed for the Heart to Health study [50]. The lifestyle intervention consists of three sessions of interactive, tailored information on the web (up to three hours of interventional contact). In previous studies, offering patients a risk-reducing strategy was associated with increased adherence and reduced CHD risk [51]. Therefore, a library of over 100 web pages providing advice on physical activity, diet, smoking and medication are tailored according to participants’ selection of risk-reducing strategies (the web pages are available from the authors on request). Each session may last up to 60 min in duration depending on participants’ individual pace with sessions delivered at monthly intervals. The first session begins with content-specific education on diet, physical activity and smoking cessation. This session also includes tips on how to overcome self-identified barriers to risk reduction and the creation of steps toward self-identified actionable goals. Sessions 2 and 3 include similar content; a participant begins by reviewing their progress toward goals, continues with education and tips to overcome barriers and finishes with identification of new goals [50].

### Follow-up assessment

Follow-up assessments take place at 12 weeks after randomisation and include an online questionnaire, physical activity monitoring and blood sample collection. Not all of the measures in the baseline questionnaire are repeated at follow up (Table 2). The follow-up questionnaire (available from the authors on request) should take no more than 20 min to complete. Participants are requested to complete this follow-up questionnaire and will receive two reminder emails at day 7 and day 14 after sending the follow-up questionnaire if it has not been completed. If we do not hear from participants by day 24, we will mark the data as missing.

**Table 2 Tab2:** INFORM measures at each stage of the study

	Measure or Instrument name	INTERVAL	INFORM baseline	INFORM follow-up	Mode of assessment	Note
Primary outcome	Physical Activity Level*	✓	✓	✓	accelerometers	using the Axivity AX3 – 3Axis logging Accelerometer®
Secondary outcomes	Traditional risk factors					
	Fruit and vegetables intake	✓		✓	carotenoids	
	Weight		✓	✓	self-report	as used in Godino et al. [56] and Knowles et al. [48]
	Cholesterol Panel (total, HDL and LDL cholesterol, triglycerides)	✓		✓	blood serum	
	Fructosamine	✓		✓	blood serum	
	Nutrition Behaviour (fruit, vegetables, whole grains, fish, red and processed meat)		✓	✓	self-report	one-item questions that reflect the present prevention guidelines on CVD [16, 10]
	Physical Activity Level		✓	✓	self-report	EPIC-Norfolk Physical Activity Questionnaire [60]
	Smoking Status		✓	✓	self-report	
	Alcohol Consumption		✓	✓	self-report	
	Current Medication and Healthcare Usage		✓	✓	self-report	adapted version of the Health Services Research Unit Aberdeen questionnaire [61]
	Perceived risk					
	Comparative and Absolute Cardiovascular Risk		✓	✓	self-report	adapted according to Diefenbach et al. [62] and used in other risk communication studies [48, 56]
	Cognitive evaluation of provision of coronary heart disease risk scores					
	Understanding of Risk Scores			✓	self-report	as used in another trial of risk communication [56]
	Perceived Accuracy of Risk Scores			✓	self-report	as used in other risk communication studies [48, 56]
	Acceptability of the Intervention			✓	self-report	in line with the Heart to Health study [50]
	Psychological outcomes					
	Stress		✓	✓	self-report	as used in the Randomized Trial of Personal Genomics for preventive cardiology [48]
	Mood		✓	✓	self-report	adapted from the Patient Health Questionnaire [63]
	Coronary Heart Disease-related Worry		✓	✓	self-report	an adaptation of the Cancer Related Worry Scale [64]
	Genetic Risk-related Worry/Anxiety		✓		self-report	as used by Knowles et al. [48]
Moderators and mediators	Sociodemographic characteristics					
	Sex, Age, Ethnicity	✓			self-report	
	Marital Status		✓		self-report	
	Socioeconomic Status (level of education, level of income, living area)		✓		self-report	adapted from the European Health Interview Survey; deprivation level of the area based on the Index of Multiple Deprivation, Department for Communities and Local Government
	Numeracy Skills		✓		self-report	3-item Schwartz scale [65]
	Family History of Coronary Heart Disease		✓		self-report	
	History of Genetic Testing		✓		self-report	
	History of Coronary Heart Disease Risk Assessment		✓		self-report	
	Self-rated Health		✓	✓	self-report	Ware et al. [66]
	Barriers to risk-reducing strategy		✓		self-report	in line with the Heart to Health study [50]
	Cognitive and emotional theory-based antecedents to behaviour change					
	Intentions		✓		self-report	adapted according to Ajzen [67] and used in previous similar research [56]
	Perception of Diet		✓		self-report	
	Perception of Physical Activity		✓		self-report	
	Coronary heart disease risk Representations		✓		self-report	the Brief Illness Perceptions Questionnaire [68]
	Self-efficacy		✓		self-report	as used in previous behavioural research [56, 68]
	Response Efficacy		✓	✓	self-report	as used in previous behavioural research [52, 69]
	Social Support		✓		self-report	the Multidimensional Scale of Perceived Social Support [70]
	Time Orientation		✓		self-report	as used in a study by Peretti-Watel et al. [71]
	Sense of Coherence		✓		self-report	3-items scale, Lundberg et al. [72]
	Comparative Optimism		✓		self-report	comparative perceived risk

*participants who did not take part in physical activity monitoring during the INTERVAL Study will be required to undertake baseline activity monitoring over 7 days

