### Baseline assessment

Baseline information is collected prior to randomisation. Responders who are eligible to take part in the INFORM study and provide informed consent are sent a welcome email message with an individually tagged URL link to the baseline online questionnaire (available from the authors on request). Participants are requested to complete this questionnaire within 7 days and receive reminder email messages at day 7 and day 14. A reminder telephone call will be made on day 16 if the questionnaire still has not been completed. The measures assessed in the baseline questionnaire are combined with several measures taken during the participants’ INTERVAL study assessment in order to characterise the study population and to calculate individual’s phenotypic and genetic risk scores.

For consenting participants in INFORM who took part in physical activity monitoring in the INTERVAL study, physical activity data will be shared between studies and used as a baseline measurement for the INFORM study. Participants who did not take part in physical activity monitoring during the INTERVAL study are required to undertake baseline physical activity monitoring over 7 days. The study team sends participants a watch-like device (Axivity AX3 3-Axis Logging Accelerometer®) to measure physical activity over a period of 7 days. The device is sent together with instructions and a list of frequently asked questions and responses to the questions. A letter detailing the “switch on” and “switch off” date (pre-set by the study team before posting) is included with the device with instructions for return to the study team in the freepost envelope provided. Participants are reminded by email to return their monitor 6 days after the “switch off” date. If the monitor is not returned after the email message is received, the helpdesk will attempt to contact the participant by telephone or email. If a response is still not received, a written request for the return of the monitor will be sent after 5 weeks. If the monitor is still not returned after 6 weeks, the participant is randomised.

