#### Follow-up physical activity monitoring

All participants are requested to complete physical activity monitoring for 7 days at the 12-week time point following the same procedure as at baseline.

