#### Blood sample

All participants are asked to provide a blood sample, which is taken at their general practice. The blood sample is used to provide information on participants’ lipid panel (total, HDL and low-density lipoprotein – LDL – cholesterol; triglycerides), carotenoid levels and fructosamine level. The study coordination team provides a blood sample kit (Royal Mail Safebox™) which is sent to participants along with the follow-up physical activity monitor. The blood sample kit includes blood collection tubes with barcoded, anonymised participant study number, instructions for general practice clinicians, general practice invoicing instructions and appropriate packaging addressed to the receiving central laboratory with pre-paid postage. A staff member at the participant’s general practice takes verbal consent for the procedure at the time it is taken, writes the date and time that the sample was taken on the blood collection tube, packs the sample, and enters it into the postal delivery chain alongside regular practice post. Samples are transported by Royal Mail first class mail to a central laboratory (UK BioCentre, Stockport, Cheshire, UK) that logs and processes the samples. An email reminder message to have a blood sample taken is sent 10 days after the sample kit has been posted. The helpdesk attempts to contact participants with outstanding blood samples on days 17 and 28 after the sample kit has been posted, and if the sample is not received after 31 days after the sample kit has been posted, blood sample results will be marked as missing data.

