#### Analysis design – randomised controlled trial

All trial analyses will be based on the Intention To Treat (ITT) principle. Those with missing follow-up data will be excluded from the analyses (a complete case approach). We will perform sensitivity analyses to assess the impact of missing follow-up data on the results. Participants with missing baseline data will be included in the analyses using the missing-indicator method [59].

The null hypothesis for the primary analysis is that there is no difference between any of Groups 1 to 4. Estimates of the following pairwise differences will be calculated: 1) Group 1 (control group) vs. Group 2 (lifestyle advice only) – to estimate the effect of providing lifestyle advice compared with no intervention; 2) Group 3 (phenotypic risk score and lifestyle advice) vs. Group 4 (phenotypic and genetic risk scores and lifestyle advice) – to estimate the effect of providing a genetic risk score in addition to lifestyle advice and a phenotypic risk score; 3) Group 3 + Group 4 vs. Group 1 – to estimate the effect of providing risk score information and lifestyle advice compared with no intervention, and 4) Group 3 + Group 4 vs. Group 2 – to estimate the effect of providing risk score information in addition to lifestyle advice.

Mean changes in objectively measured physical activity between baseline and 3-month follow-up will be analysed using analysis of covariance (ANCOVA). The ANCOVA model will model change (follow-up minus baseline) in objectively measured physical activity, adjusted for baseline. A test involving three degrees of freedom (3 d.f.) will be performed of the null hypothesis that there is no difference between the four randomised groups. If the p-value from this test is <0.01, this will imply that there are differences between the groups. The ANCOVA model will also be used to derive estimates of the differences in mean change and 95 % confidence intervals for each of the four pairwise comparisons described above. To avoid detracting the focus of the results from the overall 3 d.f. test, *p*-values for each of the pairwise comparisons will not be calculated.

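### The follow-up questionnaire, the only systematic quantitative measure of psychological outcomes and healthcare use, has the lightest stated pursuit of the follow-up collections

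*Protocol article*

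**What the plan says.** All places are in the Protocol article.

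- **Follow-up questionnaire** (Follow-up assessment). "Follow-up assessments take place at 12 weeks after randomisation". Participants "will receive two reminder emails at day 7 and day 14 after sending the follow-up questionnaire if it has not been completed". The sequence then ends: "If we do not hear from participants by day 24, we will mark the data as missing". No telephone call is listed.
- **Baseline questionnaire** (Baseline assessment). Emails go out at the same two days, and then "A reminder telephone call will be made on day 16 if the questionnaire still has not been completed".
- **Follow-up blood sample** (Blood sample). After an email at day 10, "The helpdesk attempts to contact participants with outstanding blood samples on days 17 and 28 after the sample kit has been posted". The result is set to missing if nothing has arrived by day 31.
- **Activity monitor** (Baseline assessment; Follow-up physical activity monitoring). An unreturned monitor leads to an email, after which "the helpdesk will attempt to contact the participant by telephone or email", and then to a letter at 5 weeks. Follow-up monitoring is done "following the same procedure as at baseline".
- **Outcomes concerned** (Table 2; Measures). Stress, mood, CHD-related worry, perceived risk, and medication and healthcare use are self-report only.
- **Other capture of harm** (Adverse events). There is no formal monitoring. Events that come to the team's attention incidentally are recorded.
- **Analysis** (Analysis design – randomised controlled trial). "Those with missing follow-up data will be excluded from the analyses (a complete case approach". The next sentence plans sensitivity analyses for missing follow-up data, without naming a method.

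**The concern.** The Discussion gives possible harm, such as raised anxiety or false reassurance, as one of the gaps that this trial addresses. The questionnaire is where such harm would be seen in randomised comparison, yet of the follow-up collections it is the one the article pursues least.

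The trial is open, so a participant's willingness to answer can depend on what they were told. If people upset by a risk score are less likely to reply, and this differs between arms, a complete-case comparison tends to understate harm. Even without such a pattern, losing replies that a call might have obtained costs precision on outcomes that must reach p<0.001 to be regarded as convincing (Multiplicity).

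**Working it through.** **1. Stated pursuit, side by side**

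| Collection | Email | Personal contact | Closure |
|---|---|---|---|
| Baseline questionnaire | days 7, 14 | call, day 16 | none stated |
| Follow-up questionnaire | days 7, 14 | none listed | day 24 |
| Follow-up blood sample | day 10 | helpdesk, days 17 and 28 | after day 31 |
| Monitor | 6 days after switch-off | telephone or email, then letter at 5 weeks | none stated for follow-up |

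The monitor steps are written for baseline. Their 6-week step ends in randomisation, so it cannot carry over to follow-up and is not used here. Blood-sample days count from posting of the kit, and the questionnaire reminders count from sending of the questionnaire. Comparing day 24 with day 31 assumes that both go out at about the same time.

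**2. The plan's own figure for loss**

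The sample size section gives 186 per group and 20% attrition. 186 / (1 − 0.20) = 232.5, rounded up to 233, and 4 × 233 = 932, as stated. The plan therefore allows for about 0.20 × 233 = 46.6, or 47 people per group, without follow-up. This allowance was made for the accelerometer outcome. No response rate is given for the questionnaire, so 20% is an assumption below.

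**3. Size of a possible bias**

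Let m be the missing share, equal in two arms A and B, and let g be the mean of non-responders minus the mean of responders within an arm, in SD units. The complete-case mean differs from the full mean by −m × g, so:

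bias in the A − B difference = −m × (g_A − g_B)

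If g_A = g_B, the bias is zero. Otherwise, with m = 0.20 and assumed differential gaps:

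| g_A − g_B (SD) | Size of bias (SD) | Actual coverage of a 95% interval |
|---|---|---|
| 0.25 | 0.20 × 0.25 = 0.05 | about 92% |
| 0.5 | 0.20 × 0.5 = 0.10 | about 84% |
| 1.0 | 0.20 × 1.0 = 0.20 | about 51% |

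For scale, the 95% interval half-width with 186 per group is 1.96 × √(2/186) = 0.203 SD.

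**4. What recovering half the non-responders would do**

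- If those recovered resemble those still missing, m falls to 0.10 and a differential gap of 0.5 SD gives 0.10 × 0.5 = 0.05 SD, half the bias.
- If those recovered resemble responders, the remaining 10% carry the whole gap, which becomes 1.0 SD. The bias is 0.10 × 1.0 = 0.10 SD, unchanged.
- For a binary outcome, the room that missing answers leave in the group difference falls from ±20 to ±10 percentage points, whoever is recovered.
- Responders rise from 186 to about 0.90 × 233 = 210 per group, and √(186/210) = 0.94, so intervals narrow by about 6%.

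**The case against.** **The article may simply not mention a call.** It condenses a fuller protocol and does not rule one out. This has some force. However, the Follow-up assessment section gives a sequence that runs to a cut-off, and the article names telephone or helpdesk contact where it applies to the other collections. The day-24 rule itself is stated outright.

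**The comparators are not alike.** The baseline questionnaire feeds the risk scores, a blood sample needs a practice visit and postage, and chasing a monitor recovers a device whose recording is already made. A tight questionnaire window also keeps answers close to 12 weeks. These are fair reasons for some difference. They do not explain why helpdesk staff already contacting a participant about blood should not also ask for the questionnaire.

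**Sensitivity analyses are planned.** This stands, and the complete-case result is not left unchecked. Those analyses vary assumptions about the missing answers. They do not supply the answers.

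**Late replies carry a risk of their own.** Under Interventions, every participant, controls included, receives the omitted information at the end of follow-up. A control who replies after that has been exposed to what is being tested. This stands and limits the fix.

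**Stronger readings are not supported.** A reader might infer that harm is measured nowhere else. Interviews, focus groups and incidental reports also exist, though only for a purposive subset or by chance contact. A reader might also infer that non-response is known to be related to distress and to hide harm. The document gives no evidence or figure for that, and the follow-up procedure is not described as differing between arms.

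**Conclusion.** The point holds as a low-cost improvement of modest weight. The article sets the lightest stated pursuit for the one systematic quantitative measure of psychological outcomes and healthcare use, and gives no reason for it. The primary and key secondary outcomes do not depend on this questionnaire.

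No bias has been shown. The 0.05 to 0.20 SD range rests on three assumptions: 20% missing in each arm, a responder/non-responder gap that differs between arms, and a difference in that gap of 0.25 to 1.0 SD. Better pursuit is sure to help precision and to narrow worst-case bounds to the extent that it recovers replies. It reduces bias only if at least some of those recovered resemble those still missing.

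**What to change.** In the Follow-up assessment section:

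1. Add the day-16 telephone reminder already used at baseline.
2. Have the helpdesk ask for an outstanding questionnaire at its existing day-17 and day-28 blood-sample contacts.
3. Accept questionnaires until the blood-sample window closes (day 31), provided that they are completed before the participant receives the withheld information described under Interventions.
4. Record the completion date, keep these replies in the main analysis, and exclude replies after day 24 in a sensitivity analysis.

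The cost is some extra helpdesk calls by existing staff, a slightly wider spread of assessment times, and the need to hold back the withheld information until the questionnaire is returned or the window closes.

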#### Follow-up physical activity monitoring

All participants are requested to complete physical activity monitoring for 7 days at the 12-week time point following the same procedure as at baseline.

#### Blood sample

All participants are asked to provide a blood sample, which is taken at their general practice. The blood sample is used to provide information on participants’ lipid panel (total, HDL and low-density lipoprotein – LDL – cholesterol; triglycerides), carotenoid levels and fructosamine level. The study coordination team provides a blood sample kit (Royal Mail Safebox™) which is sent to participants along with the follow-up physical activity monitor. The blood sample kit includes blood collection tubes with barcoded, anonymised participant study number, instructions for general practice clinicians, general practice invoicing instructions and appropriate packaging addressed to the receiving central laboratory with pre-paid postage. A staff member at the participant’s general practice takes verbal consent for the procedure at the time it is taken, writes the date and time that the sample was taken on the blood collection tube, packs the sample, and enters it into the postal delivery chain alongside regular practice post. Samples are transported by Royal Mail first class mail to a central laboratory (UK BioCentre, Stockport, Cheshire, UK) that logs and processes the samples. An email reminder message to have a blood sample taken is sent 10 days after the sample kit has been posted. The helpdesk attempts to contact participants with outstanding blood samples on days 17 and 28 after the sample kit has been posted, and if the sample is not received after 31 days after the sample kit has been posted, blood sample results will be marked as missing data.

### Measures

Table 2 provides details of the measures collected in the INFORM study and the stage of the study at which each is assessed. The primary outcome is objectively measured physical activity, defined as average acceleration (m/s^2^) over the observation period. Participants are instructed to continuously wear the accelerometer for 7 consecutive days and nights, and to carry on with all normal activities during this time. The accelerometers are waterproof and can be worn while swimming and showering. Accelerometers have been chosen as a measure of physical activity because they cause low participant burden and are not subject to the reporting bias or recall problems associated with the self-report methods [52].

The key secondary outcome, dietary behaviour, is objectively measured by levels of six serum carotenoids (alpha-carotene, beta-carotene, lutein, lycopene, beta-cryptoxanthin, zeaxanthin). Carotenoids are biologically active pigments in plants but are not synthesised in animals and as such they represent a valid biomarker of vegetable and fruit intake [53].

Other objectively measured secondary outcomes include total, HDL and LDL cholesterol and fructosamine. We also collect self-reported secondary outcomes via an online questionnaire. They include cardiovascular risk factors (self-reported weight, smoking status, alcohol consumption, physical activity and dietary behaviour); current medication and healthcare usage; perceived risk (perception of comparative and absolute risk); cognitive evaluation of provision of CHD risk scores (understanding, accuracy, acceptability); and psychological outcomes (anxiety associated with testing, fatalism, depression, stress and mood).

As with any other intervention, it is important to understand the mechanisms that explain why the provision of CVD risk information leads to change or not, and whether there are people with certain characteristics who may benefit more or less from CVD risk communication. To understand this, the following potential moderators and mediators of the relationship between provision of risk information and behaviour change are being measured as part of the INFORM study: a) sociodemographic characteristics (ethnicity, socioeconomic status, education, income, numeracy skills and marital status); b) history of genetic testing and CHD risk assessment; c) self-rated health; d) cognitive and emotional theory-based antecedents to behaviour change (behavioural intentions, perception of diet and physical activity, beliefs about CVD, self-efficacy and response efficacy, social support, mood and personality characteristics); and f) personal barriers to risk reducing strategies.

